#### Health Behavior Change Support Program

After referral, participants will enter into a program of health behavior change support for an average of three to six sessions over a period of up to 12 months. The completion of three sessions has been identified as sufficient time to progress key aspects of the HCA approach and achieve a moderately intensive program. These sessions will be held with Lifestyle Advisors who are fitness professionals and experienced leaders in the Heart Foundation “Heartmoves” program [29]. The Lifestyle Advisors will undertake training in the HCA approach to health change, and receive ongoing professional development sessions from HCA staff.

A short summary report will be provided back to the patient’s GP after the baseline, third, and final sessions. The advisors will connect patients with existing community resources, such as lifestyle modification programs and services to support their behavior change goals as appropriate. The advisors will also work to build relationships with local community-based providers to ensure they meet the needs of their patient cohort, and support the providers to develop systems to achieve better linkages to general practice.

#### Building an Improved Cardiovascular Disease Prevention System

Support to develop better systems for prevention of CVD will be provided to the general practice, allied health, and community sectors involved in the intervention. These activities align broadly with the elements of the ECCM. The table below provides a summary of these activities, and was based on a similar table developed for the Racial and Ethnic Approaches to Community Health program [10].

**Table 1 table1:** Summary of *HeartLink* activities.

ECCM element	General practice activities	Community sector activities (outside general practice)
Decision support	Professional development on a CVAR assessment and management guidelines for all general practice staff.	Professional development on relevant aspects of CVAR assessment and management for allied health and lifestyle modification program providers.
	Identify decision support strategies for CVAR guidelines implementation using clinical software and complementary resources.	Identify and support the role of community-based providers in supporting the assessment and management of CVAR.
Information systems	Undertake ongoing quality activities to improve risk factor data collection and recording.	Review community and allied health information systems and identify opportunities for quality improvements related to relevant aspects of CVAR risk assessment and management.
	Develop reporting, recall, and monitoring processes for CVAR assessment of the patient population.	Identify community information systems to support community sector decision making.
Delivery system design/ reorientate health services	Develop mechanisms to improve linkages between general practices and the allied health and community sector lifestyle modification services.	Develop mechanisms to improve linkages between community sector and allied health lifestyle modification services with general practices.
	Promote the role of general practice in prevention of CVD to practice populations.	Promote the role of allied health and community sector lifestyle modification services in CVD prevention.
Self-management/ develop personal skills	Lifestyle Advisor service to provide the connection between the patient, general practice, and the community sector.	Develop and support a network of community-based lifestyle related service providers with an interest in CVD prevention.
	Deliver professional development activities to improve the health behavior change skills of general practice staff.	Deliver professional development activity to improve health behavior change skills of community sector lifestyle providers and allied health professionals.
Build healthy public policy	Map relevant national and local policy to understand aspects that support or impede the intervention approach.	Map relevant local and national policy and programs to understand aspects of policy that support and impede the intervention approach.
Create supportive environments	Promote community initiatives that are working to create supportive environments for healthy lifestyles in the general practice setting.	Develop connections with existing community initiatives that are working to create supportive environments for healthy lifestyles.
Strengthen community action	Promote the *HeartLink* intervention activities through general practice populations.	Promote the *HeartLink* intervention to the community through various media and community network channels.
	Provide opportunities to create connections between health care professionals and community organizations.	Provide opportunities to create connections between community organizations and health care professionals.

### Data Collection

#### Primary Health Outcome Measure

The primary health outcome measure for the study will be the change in the CVAR percentage score for the *HeartLink* intervention participants. A range of patient-reported health and well being outcomes will also be examined, including physical activity levels, fruit and vegetable intake, CVD medication adherence, health related quality of life, generalized self-efficacy, and intention to change key health behaviors related to CVD risk reduction.

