#### One-Group Pre/Post Quasi-Experimental Design

The second component, the *HeartLink* intervention, uses a preexperimental, one group pre/post test design. A single cohort of patients 45-74 years old (or 35-74 years old if Aboriginal and/or Torres Strait Islander) considered to be at high risk for a CVD event within the next five years will be recruited through general practices, and provided with enhanced usual care and additional health behavior change support. CVAR for each patient will be determined using the Australian adaption of the Framingham based CVD risk score, with high risk being defined as a CVAR > 15% over the next 5 years [4].

The design has been informed by interventions in Australia and the United Kingdom, which also aimed to achieve CVD risk reduction through enhanced risk identification and reduction programs in primary health care [23-25]. *HeartLink* will use the ECCM as a framework to create improved prevention pathways in the primary health care sector, including providers of lifestyle modification services and programs outside the traditional health sector.

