### HeartLink Participant Eligibility and Recruitment

Inclusion and exclusion criteria for *HeartLink* were established. Patients needed to be 45-74 years old (35-74 years old for Aboriginal and/or Torres Strait Islander people), have a CVAR >15% over the next five years, and an absence of established CVD, diabetes, or a previous cardiovascular event
to be included. Patients were excluded if they had not attended the general practice in the last two years, had a complex coexisting medical condition or impairment, were non-English speaking, or were excluded from the intervention by their general practitioner.

The patients participating in the intervention will be recruited through their usual general practice. Each of the pilot general practices uses a clinical software program to manage patient information and possesses a clinical audit tool. The clinical audit tool has a CVD risk calculator report function that generates a list of patients (from the clinical software records) meeting the CVAR inclusion criterion of associated risk level. The CVAR calculator uses age, gender, systolic blood pressure, smoking status, and serum lipids to calculate risk. A history of left ventricular hypertrophy and having diabetes are also identified.

An initial list of patients with a CVAR > 15% will be generated for each practice, and from this list random subsamples in batches of around 20 patients (the actual number depending on practice size and available resource) will be generated at scheduled intervals. As each sample is identified, the invitation letters will be posted (with up to two reminders) to invite participants to attend their practice for a “heart and stroke check”. Those attending the practice for the check will be offered participation in a health behavior change program if they are eligible. The scheduled sampling will occur over a six month period until the target sample size is achieved. Figure 2 shows the *HeartLink* participant pathway.

The University of Canberra’s Human Research Ethics Committee approved this study (Project number 11-141).

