### HeartLink Intervention Description

#### Enhanced Usual Care in General Practice for Patients at High Risk of Cardiovascular Disease

The aims of the *HeartLink* pilot are to work with general practices to enhance care in relation to identification, recall, assessment, and management of patients at high risk of CVD. The intervention follows the evidence-based “5A’s” approach, with key steps integrated across the pilot design [26]. Upon recruitment, support will be provided to all of the participating general practices to audit their patient data, establish or improve data quality processes, and, where required, encourage processes to improve the levels of preventative activities such as measurement and recording of patient blood pressure. These actions are expected to maximize the patient numbers for recruitment, and will support the broader aims of the pilot to improve systems for the prevention and management of CVD in the pilot practices.

The PEN Computer Systems Pty Clinical Audit Tool CVD risk report will be used for the population of each practice, except those not attending the practice for more than two years, as it is likely that they are no longer patients of the practice or do not have a regular general practitioner (GP) at the practice. The patients identified as having a risk score of >15% on their most recently recorded clinical information will be sent a letter asking them to visit for a “heart and stroke” check [4]. The patients whose most recent cholesterol measures are greater than six months old will be sent a pathology request form along with their recall letter to encourage them to update their lipid levels before they attend their recall visit.

When patients arrive for their recall visit, they will have their CVAR recalculated by the practice nurse before a consultation with their GP.

As part of the recall visit to the general practice at baseline and 12 months, the CVD risk factor information required to calculate the absolute risk will be collected. The practice nurse in the clinical environment will measure the blood pressure, and the cholesterol level measurement (total and high-density lipoprotein cholesterol) will have been undertaken by a commercial pathology service provider upon referral from the GP prior to the visit. The smoking status, defined as smoker or nonsmoker (self-reported), will be recorded.

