### Data Analysis

#### Quantitative Data Analysis

Changes in the CVAR will be reported at the total practice population level, but also analyzed by each practice. The primary analysis will be done on an Intention to Treat basis. The CVAR was chosen as the primary health outcome, as it represents an all around measure of the *HeartLink* intervention’s ability to meet its objectives.

An analysis of the quantitative data collected from the clinical data and the participant survey will be undertaken. Univariate comparisons between the pre and post intervention groups will be conducted using a chi-square test for equal proportion (or Fisher’s exact tests where numbers are small), and reported as numbers and percentages. Continuous normally distributed variables will be compared using student’s *t* tests and reported as means (95% confidence interval). Nonnormally distributed data will be compared using Wilcoxon signed rank tests.

The *HeartLink* pilot data will be used to estimate population proportions (and confidence intervals) for those at high risk of CVD in the ACT. This data will also generate planning information for a future larger study. The intercluster correlation coefficient, effect size, and standard deviation will be examined to help determine sample size calculations, cluster size, and number of clusters.

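### The primary outcome is the raw 12-month change in a risk score that takes age as an input, so in this one-group design a year of ageing enters the estimate with nothing to cancel it

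*Protocol article*

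**What the plan says.** Under Primary Health Outcome Measure: "The primary health outcome measure for the study will be the change in the CVAR percentage score". Under HeartLink Participant Eligibility and Recruitment, the inputs are listed: "The CVAR calculator uses age, gender, systolic blood pressure, smoking status, and serum lipids to calculate risk". The design section names the equation, "CVAR for each patient will be determined using the Australian adaption of the Framingham based CVD risk score", and sets the entry level, with "high risk being defined as a CVAR > 15% over the next 5 years". The section on enhanced usual care fixes the two occasions: "at baseline and 12 months, the CVD risk factor information required to calculate the absolute risk will be collected". It also says that the practice nurse recalculates CVAR at the recall visit. The design "uses a preexperimental, one group pre/post test design".

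Quantitative Data Analysis plans simple comparisons of before with after and gives the reason for the outcome: "The CVAR was chosen as the primary health outcome, as it represents an all around measure" of whether HeartLink meets its objectives. The estimate has two stated uses. The second study aim is to measure efficacy in the six practices, and the sample size section expects the pilot to supply a possible effect size for the full trial. The article nowhere says that age is held at its baseline value or that an expected ageing increment is subtracted. The limitations section covers scale, opt-in practices, a single city and uneven standardization. It looks ahead to a controlled trial, but lists neither ageing nor the missing comparator as a limitation of this estimate.

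**The concern.** In a randomized comparison both arms age equally, and the age term in the score largely drops out of the contrast. Here the contrast is each patient against the same patient a year earlier, so the age term stays in. The reported change then mixes two things: movement in the modifiable risk factors, which HeartLink targets, and the passage of a year, which it cannot alter.

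Two uses of the result are affected. The efficacy estimate carries an upward component unrelated to the intervention. The planning effect size carries a component that would be largely absent from the between-arm contrast of the cluster randomized trial it is meant to plan, so that trial could be sized on the wrong quantity.

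**Working it through.** **Inputs from the article.** Outcome: change in CVAR. Score inputs: age, gender, systolic blood pressure, smoking, lipids. Interval: 12 months. Entry level: CVAR above 15% over 5 years. Sample: 6 practices × 30 = 180, which reproduces the stated total. The article gives no age coefficient, no SD of change, no significance level and no target effect.

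**Assumptions.** The score rises with age, taken as a property of a Framingham-type absolute risk; the article does not spell this out. The rate of rise, the SD of change, a two-sided 0.05 level and a 2-point true fall are all assumed for illustration.

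**Step 1: decomposition.** Write C(a, x) for the score at age a with risk factors x, where x0 is the baseline value and x1 the 12-month value. Then

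C(a+1, x1) − C(a, x0) = [C(a+1, x1) − C(a, x1)] + [C(a, x1) − C(a, x0)].

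The first bracket is the ageing component. The second is the change at fixed age. Calculating the 12-month score at baseline age makes the first bracket zero by construction.

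**Step 2: size with risk factors unchanged.** If CVAR rises by 3% to 6% relative per year of age:

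- at CVAR 15%: 15 × 0.03 = 0.45 to 15 × 0.06 = 0.90 points.

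A second form puts the assumed relative rise g on the 5-year cumulative hazard: drift = [1 − (1 − r0)^(1+g)] − r0. With r0 = 0.15 and g from 3% to 9%, it gives +0.41 to +1.23 points. With r0 = 0.25 it gives +0.64 to +1.92. Both forms depend on the assumed rate.

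**Step 3: against the precision of the pilot.** If all 180 patients have both scores and the SD of change is 4 to 6 points, the 95% half-width is 1.96 × 4/√180 = 0.58 to 1.96 × 6/√180 = 0.88 points. The drift is therefore of the same order as the precision. With no true effect and no other bias, the probability that a paired test gives a nominally significant result, almost always a rise, is:

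| Drift (points) | SD 4 | SD 6 |
|---|---|---|
| 0.4 | 0.269 | 0.145 |
| 0.8 | 0.765 | 0.432 |

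**Step 4: effect on planning.** Take an assumed true fall of 2 points, from 15% to 13% at fixed age. The ageing component now applies at 13%: 13 × 0.03 = 0.39 to 13 × 0.06 = 0.78. The raw fall is 2 − 0.39 = 1.61 to 2 − 0.78 = 1.22, so 0.39/2 = 20% to 0.78/2 = 39% of the fall is hidden. Required sample size scales with 1/effect², so planning on the raw change would multiply it by (2/1.61)² = 1.5 to (2/1.22)² = 2.7. A larger assumed fall would shrink these figures.

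**The case against.** The strongest reply has four parts.

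- **The derivation is open.** The article names the outcome and the occasions, but does not say which age enters the 12-month score. A full protocol or analysis plan could settle it. This stands as a caution. Still, recalculation from the information collected at 12 months naturally uses attained age, and that is the outcome as it now reads.
- **Attained-age risk is a legitimate quantity.** The article chose CVAR as an overall measure and does not claim to isolate modifiable risk. That is fair, and it is a reason to keep the attained-age change as a secondary result. It is a poor measure of what the intervention achieved when nobody is there for comparison.
- **This is a pilot.** It has no stated power and no success threshold, and its successor would be randomized. This lowers the stakes, but efficacy and a planning effect size are both declared uses.
- **The size is wholly assumed.** This stands: the documents cannot show that the drift is material.

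Three stronger readings are tempting and are not supported.

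- A reader might infer that the trial's result will, on balance, understate benefit. Patients are listed because a recorded CVAR exceeded 15%, so regression to the mean may push the change downwards. Recalculation at the recall visit may reduce this but is not shown to remove it.
- A reader might infer that practices with higher-risk patients will look worse. At 3% to 6%, the increment differs between CVAR 15% and 18% by only 0.54 − 0.45 = 0.09 to 1.08 − 0.90 = 0.18 points. The standard error of a practice mean with 30 patients is about 4/√30 = 0.7 to 6/√30 = 1.1 points (SD assumed), and the article plans no ranking of practices.
- A reader might infer that someone who enters at 74 is later scored outside the study's age range. But "Patients needed to be 45-74 years old (35-74 years old for Aboriginal and/or Torres Strait Islander people") describes entry, and the article states no age limit for the 12-month score.

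**Conclusion.** The point holds in a limited form. Age is in the score, a year separates the two scores, there is no comparator, and nothing in the article fixes age. As written, the primary outcome therefore contains an upward ageing component that the intervention cannot influence. By itself it biases the efficacy estimate and the planning effect size towards no benefit. With risk factors unchanged it is about +0.45 to +0.90 points at CVAR 15%, on the assumption of a 3% to 6% relative rise per year of age; the documents neither confirm nor exclude that rate. The overall direction of bias in the uncontrolled change is unknown. The case for acting is that this component is systematic and can be removed exactly at almost no cost, not that it has been shown to be large.

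**What to change.** Define the primary outcome as CVAR at 12 months, calculated with age held at its baseline value, minus the baseline CVAR recalculated at the recall visit. Report the attained-age change as a secondary result. Use the age-fixed change, with its SD, when planning the cluster randomized trial. Add to the limitations that a change measured without a control group remains open to regression to the mean and secular change. Removing the ageing term leaves those untouched, so the age-fixed figure may still overstate benefit.

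The cost is a sentence or two of wording and one extra calculation per patient from inputs already collected. The Results section says that post-intervention data collection is under way, so no procedure at the practices has to change. The downside is that the age-fixed figure is no longer the patient's actual absolute risk at 12 months, which is why the attained-age result should stay in the report.

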#### Individual Health and Well Being Data

Health related data will be collected from all *HeartLink* patients using validated tools via a paper-based survey administered at baseline and at 12 months. The survey will determine: (1) Physical activity levels, the usual physical activity levels will be collected via the Active Australia survey, which has been reported as reliable and having acceptable validity within an adult Australian population [30]. (2) Fruit and vegetable intake, the number of servings of fruit and vegetables will be assessed using validated questions from the National Nutrition Survey [31]. (3) Medication adherence, the participant’s adherence to the prescribed medication (antihypertensive and lipid lowering medication) is an important factor in reducing cardiovascular risk [32]. The participant’s adherence to CVD related medication (if medication has been prescribed) will be assessed using the four-item Morisky scale for each category of medication [33]. (4) Quality of life, the health related quality of life will be assessed using the short form (SF)-12v2 Health Survey (SF12 v2). The SF12 v2 is a validated and commonly used tool that provides insight into mental and physical functioning and overall health related quality of life [34]. (5) Generalized self-efficacy measure, a validated generalized self-efficacy measure, the General Self-Efficacy Scale will be used, as self-efficacy is an important determinant of behavior change. While a number of tools have been developed to measure self-efficacy in relation to specific health promoting behaviors, a generalized self-efficacy measure was selected, given that each patient will be choosing which particular health behavior or behaviors they are ready to change [35]. And (6) Intention for lifestyle change measure, several validated questions related to key lifestyle change measures for CVD risk reduction, such as dietary changes, alcohol intake, and smoking, and based on the transtheoretical model of behavior change will be included. The lifestyle change messages are all included in the Heart Foundation printed education material provided to each intervention participant [36].

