The GP consultation will comprise the usual care in relation to the management of the patient’s CVD risk profile, including making referrals to allied health professionals or medical specialists as required. GPs and practice nurses in participating practices will be offered professional development with regards to CVAR management guidelines, and will be provided with copies of the guidelines. After the GP consultation, the patient then returns to the practice nurse to consolidate the information provided by the GP. The patients will receive a brief intervention related to lifestyle modification and medication adherence, supported by Heart Foundation print material. The practice nurse consultation will be informed by the Health Change Australia (HCA) approach to health behavior change, and will aim to improve patient readiness for lifestyle change [27,28]. *HeartLink* uses the HCA approach across the intervention to provide patients with a consistent health behavior change paradigm, reinforced at each contact.

The eligible patients will then be offered participation in the health behavior change support program. If patients do not wish to progress to the program or are deemed by their GP to be ineligible, they will be given information on other health behavior change support options and offered ongoing usual care. The eligible patients who are initially not prepared to participate in the program will be provided with an opportunity to join the program at a later stage if they recontact their general practice within the recruitment timeframe of six months. The patients who are eligible and agree to participate in the health behavior change support program will be referred to the *HeartLink* Lifestyle Advisor linked to their practice.

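### If medication adherence is analysed as a category, the planned chi-square comparison lets patients who start or stop a drug count on one side only, so the pre/post difference may move with no within-person change (minor point)

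*Protocol article*

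**What the plan says.** The section Primary Health Outcome Measure lists adherence among the patient-reported outcomes to be examined beside the primary one: "physical activity levels, fruit and vegetable intake, CVD medication adherence, health related quality of life".

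The section Individual Health and Well Being Data has the measures collected "via a paper-based survey administered at baseline and at 12 months". It names two drug categories, stating that "adherence to the prescribed medication (antihypertensive and lipid lowering medication) is an important factor in reducing cardiovascular risk". It makes the scale conditional on treatment: "adherence to CVD related medication (if medication has been prescribed) will be assessed using the four-item Morisky scale for each category of medication".

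The section Quantitative Data Analysis sets one rule per data type for the clinical and survey data together:
- Categorical: "Univariate comparisons between the pre and post intervention groups will be conducted using a chi-square test for equal proportion", or Fisher's exact test for small numbers, reported as counts and percentages.
- Normally distributed: "Continuous normally distributed variables will be compared using student’s" *t* tests, without saying paired or unpaired.
- Otherwise: "Nonnormally distributed data will be compared using Wilcoxon signed rank tests".

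No analysis set is given for adherence. The section on enhanced usual care says "The patients will receive a brief intervention related to lifestyle modification and medication adherence". It also describes a GP consultation on the patient's risk profile and an offer of guideline training to GPs and practice nurses.

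**The concern.** A patient not prescribed a drug category at baseline has no baseline adherence score for it. If that patient is prescribed the category by 12 months, the later survey yields a score with nothing to set against it. A patient whose drug is stopped is the mirror case. A chi-square or Fisher's test between a pre group and a post group takes whoever is scored at each time, so both kinds of patient count on one side only.

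The percentage adherent can then rise or fall because the treated group has a different make-up, even if every continuing patient behaves exactly as before. Adherence is a named target of the nurse's brief intervention, and the design has one group and no control. Nothing else in the design would separate such a shift from a real effect, and it could be read as a result of HeartLink.

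**Working it through.** **Inputs from the article.** Planned sample: 6 practices x 30 patients = 180, which reproduces the stated total. It is the only related figure. The article gives no proportion treated, proportion starting or stopping, or adherence level. All such values below are assumptions, with complete follow-up and no change in any continuing patient.

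**Formula.** Let n0 patients be treated at baseline with proportion p0 adherent, ns start later with proportion ps adherent, and nk stop, with proportion pk of them adherent at baseline. With no within-person change:

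12-month proportion = (n0 p0 - nk pk + ns ps) / (n0 - nk + ns)

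Apparent shift = [ns (ps - p0) - nk (pk - p0)] / (n0 - nk + ns)

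The shift is zero if starters and stoppers have the same adherence as the baseline group. Otherwise it generally is not, and its sign depends on how they differ.

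**Main illustration.** n0 = 90, p0 = 0.55, ns = 45, nk = 0.
- Starters 75% adherent: (90 x 0.55 + 45 x 0.75)/135 = (49.5 + 33.75)/135 = 61.7%. Shift +6.7 points.
- Starters 40% adherent: (49.5 + 18)/135 = 50.0%. Shift -5.0 points.

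**What the named test would show.** Chi-square without continuity correction, as z = difference / sqrt[P(1 - P)(1/90 + 1/135)], where P is the pooled proportion.
- First case: P = 132.75/225 = 0.59, standard error 0.0669, z = 1.00, p about 0.32.
- Second case: P = 117/225 = 0.52, standard error 0.0680, z = -0.74, p about 0.46.

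Neither is significant. These are the p-values the test would print. It treats the groups as independent, although the same 90 patients are in both.

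**Wider range at 180 patients.** Taking 30% to 70% treated at baseline and 20% to 60% of the rest starting:

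| Treated at baseline | Of the rest, starting | Adherent: continuing / starters | Baseline | 12 months | Shift | p |
|---|---|---|---|---|---|---|
| 50% | 40% | 60% / 80% | 54/90 = 60.0% | 83/126 = 65.9% | +5.9 | 0.38 |
| 50% | 40% | 60% / 40% | 54/90 = 60.0% | 68/126 = 54.0% | -6.0 | 0.38 |
| 30% | 60% | 60% / 80% | 32/54 = 59.3% | 93/130 = 71.5% | +12.3 | 0.10 |
| 30% | 60% | 60% / 40% | 32/54 = 59.3% | 62/130 = 47.7% | -11.6 | 0.15 |
| 30% | 60% | 50% / 90% | 27/54 = 50.0% | 95/130 = 73.1% | +23.1 | 0.003 |

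Where starters resemble continuing patients, the shift stays within 1 point of zero (rounding). At 180 patients, p falls below 0.05 only in three combinations, all with the extreme contrast of 50% against 90%.

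**Paired comparison.** Restricted to patients scored at both times, the change is 0 in every scenario, because starters and stoppers do not enter.

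**The case against.** The strongest reply is that the article describes data collection correctly, since adherence to a drug that was not prescribed cannot be scored. The analysis set for one secondary measure is also detail that a condensed article may leave to a fuller document. The first half stands: the conditional question is not at fault. The second stands in part. The article does not merely leave the analysis open. It states a categorical rule for the survey data, and that rule followed literally produces the mixing.

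The reply is also right that the same section names the signed rank test, which keeps only patients scored at both times. The article does not say whether the four-item scale will be a score or a category. If it is a non-normal score, the stated method already avoids the artefact, as a paired t test would.

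Two stronger readings are tempting and not supported:
- A reader might infer that the treated set is bound to change. The consultation is described as usual care and no prescribing change is stated. Nor is it stated whether the baseline survey comes before or after it. Programme referral follows the consultation, and the section on the behavior change program also calls an early advisor session the baseline one. If the survey is given then, drugs prescribed at the recall visit already count at baseline. Only a possible change can be claimed.
- A reader might infer that the problem is separate from the choice between a paired and an unpaired test. It is not: pairing removes the bias. What pairing leaves open is reporting, because the result would describe continuing patients without saying so and starters would go unmentioned.

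**Conclusion.** The point holds conditionally and is minor. If adherence is analysed as a category under the stated chi-square or Fisher's rule, or as a score with an unpaired t test, the pre/post difference may shift through starting and stopping alone. With the signed rank test or a paired t test it does not.

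Under the main illustrative assumptions the shift is about -5 to +7 points and not statistically significant. Across the wider assumed range it runs from about -12 to +23 points, the top end needing a very large gap between starters and continuing patients. Actual size and direction cannot be known from the article, and a reader should not infer that the adherence result will be biased, or biased toward benefit. The consequence is limited to interpreting one secondary patient-reported measure in an uncontrolled pilot. The change in absolute cardiovascular risk is not affected.

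**What to change.** For each drug category, define the pre/post adherence comparison in patients prescribed that category at both baseline and 12 months, and make it paired: McNemar's test if adherence is a category, a paired t test or the signed rank test if it is a score. State which form is used. Report separately, without a pre/post test, the number of starters with their 12-month adherence and the number of stoppers with their baseline adherence. State whether the baseline survey is completed before or after the GP consultation, so that readers can tell who counts as a starter.

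This needs about a sentence of analysis text and an extra row or two in a table, using data already planned. The cost is a smaller number of patients in this secondary comparison, and a result that applies to continuing users only.
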